# Effect of application time of 38% silver diamine fluoride solution on arresting early childhood caries in preschool children: a randomised double-blinded controlled trial protocol

**DOI:** 10.1186/s13063-022-06130-1

**Published:** 2022-03-15

## Abstract

**Background:**

To study the caries lesion activity response to topical 38% silver diamine fluoride (SDF) therapy with increasing treatment application time.

**Methods/design:**

The design is a stratified-randomised, double-blind, active-controlled, parallel-group clinical trial with nine treatment arms. The trial will involve recruiting at least 414 3- to 5-year-old kindergarten children with caries, who will receive approximately 0.004 mL of 38% SDF (the typical amount applied per the manufacturer’s instructions) to treat each caries lesion. The children will be stratified by caries status, randomised by blocks, and allocated to nine groups of SDF application times: 3, 5, 10, 15, 30, 45, 60, 120, and 180 s. The outcome measure is caries lesion activity (active/arrest) at the tooth-surface level at 6 months post-initial treatment. A calibrated dentist will conduct the blinded clinical examinations at baseline and at the 6-month follow-up. In addition, the parents will be surveyed to examine the effects of the moderating variables, such as oral hygiene, on caries lesion activity. The hypothesis is that a monotonically increasing trend can be found between the SDF application time and the proportion of caries lesions that are arrested. The Cochran-Armitage test for trends in proportions, corrected for clustering within children, will be used to determine the relationship between the exposure to SDF (the SDF application time) and the response (proportion of lesions arrested) in children, taking into consideration the effect of the moderating variables as well as the nesting of multiple caries lesions within an individual child. An EC 80 analysis (an 80% maximal concentration) will be used to determine the exposure (the SDF application time) for 80% caries lesion arrest. Bootstrap methods will be used for clustered data and will be resampled by clustering to determine the 95% confidence interval.

**Discussion:**

This study will help with determining the optimal application time for SDF treatment. It will provide an evidence-based protocol for the use of SDF to arrest tooth decay in the primary teeth of young children. The results will inform an evidence-based SDF protocol to arrest caries, which affects 573 million children with tooth decay worldwide.

**Trial registration:**

ClinicalTrials.gov NCT04655430. Registered on 7th December 2020.

**Supplementary Information:**

The online version contains supplementary material available at 10.1186/s13063-022-06130-1.

## Background

Early childhood caries (ECC), which causes pain and infection, remains a challenging problem [1]. Untreated caries will progress into the tooth pulp to eventually form a dental abscess [2]. In addition, premature tooth loss due to ECC affects oral function and dentition. Poor dentition significantly affects children’s nutrition and consequently their growth, development, and general health. ECC is particularly prevalent among socially disadvantaged children, such as those from poor families and those whose parents have low educational levels [3, 4]. However, prevailing restorative methods for preventing and treating ECC are neither available nor affordable for these children [5].

Clinical studies have demonstrated that using 38% silver diamine fluoride (SDF) prevents and arrests ECC [6] A literature review of SDF suggested that 38% SDF can be an effective agent in preventing new caries as well as arresting dental caries in the primary teeth of children [5]. Another review also concluded that SDF is an effective, efficient, and equitable caries-control agent [7]. Milgrom and Chi (2011) advocated for SDF therapy as an important prevention-centred caries management strategy during critical early childhood periods [8].

Clinicians typically apply 38% SDF solution topically to a dental caries lesion and then leave it on the tooth for a certain amount of time before washing away any excess. Studies have used arbitrary application times with no consensus. However, clinicians have recommended a range of increasing application times with no scientific evidence (Table 1). A short application time is desirable because SDF is frequently applied to very young children who have difficulty with cooperating. Often caries can affect multiple teeth, which makes SDF application even more difficult, especially in younger children. A lack of cooperation often compromises treatment or renders SDF treatment impossible or ineffective. A search found no published or registered trials on the SDF exposure time-response relationship. Thus, this study addresses an important gap in the knowledge regarding SDF treatment.

**Table 1 Tab1:** Recommendations for application protocol of silver diamine fluoride (SDF) solution

Authors, year, reference	SDF application protocol
Horst et al. 2016 *Journal of California Dental Association* 44:16–28.	Isolate the tooth with gauze Apply SDF to the caries of the tooth, and leave it for up to **60 s** Rinse with water
Crystal et al. 2017 *Pediatric Dentistry* 39:E135-E145.	Isolate the tooth with cotton rolls and/or gauze Apply SDF to the caries of the tooth, and leave it for **60 s** Dry excess SDF with a gentle flow of compressed air
Croll & Berg 2018 *Inside Dental Hygiene Continuing Education Course* (https://idh.cdeworld.com/courses/5155)	Blot-dry the surface of the carious lesion with a cotton swab and an air syringe Paint on SDF, and continue to dab it; keep lesion isolated for **60 s** Blot with cotton swab, and then, cover it with fluoride varnish
American Dental Association 2018 (https://www.youtube.com/watch?v=a0HH7GifdM4)	Clear and dry the caries of the tooth with cotton pellet and/or gauze Apply SDF to the caries of the tooth, and leave it for **60 s** Dry excess SDF with gauze if necessary
Yee et al. 2009 *Journal of Dental Research* 88:644-647.	Isolate the tooth with cotton rolls Apply SDF to the caries of the tooth, and leave it for **120 s** Remove excess via gentle blotting with cotton pellet
Clemens et al. 2018 *Journal of Public Health Dentistry* 78:63-68.	Isolate the tooth with cotton rolls and/or gauze The exposure time of SDF treatment is aimed at **120** s Remove excess SDF with gauze, and then, apply fluoride varnish
Seifo et al. 2020 *British Dental Journal* 228:75-81.	Isolate the tooth with cotton rolls Apply SDF to the caries of the tooth, and leave it for **120 s** Remove excess via gentle blotting with cotton pellet
Llodra et al. 2005 *Journal of Dental Research* 84:721-724.	Isolate the tooth with cotton rolls Apply SDF to the caries of the tooth, and leave it for **180 s** Wash with a 30s water spray three minutes after the application
Burgette et al. 2019 *Journal of Dentistry for Children* 86:32-39.	Isolate the tooth with cotton rolls and/or gauze Apply SDF to the caries of the tooth, and leave it for **180 s** Dry excess SDF, and then, apply fluoride varnish

### Aim

To determine the proportion of caries lesions arrested by topical 38% SDF therapy with increasing treatment application times.

### Objectives

The primary objective is to study the proportion of caries lesions arrested by topical 38% SDF therapy with increasing treatment application times. The secondary objective is to study staining effect (discolouration) of the caries lesion with increasing treatment application times of topical 38% SDF therapy.

### Hypothesis

A monotonically increasing trend can be found between the SDF application time and the proportion of caries lesions arrested and intensity of discolouration of carious lesion.

## Methods/design

### Trial design

This is a stratified-randomised, double-blind, active-controlled, parallel-group clinical trial with eight arms. The extension of the Consolidated Standards of Reporting Trials 2010 Statement will be followed [9]. In addition, the design and report of this protocol follow the Standard Protocol Items: Recommendations for Interventional Trials statement (Additional file 1. SPIRIT 2013 Checklist) [10]. The schedule of this study is shown in Fig. 1.

**Fig. 1 Fig1:**
[figure not shown]
Schedule of enrolment, intervention, and assessments of application time of 38% silver diamine fluoride (SDF) solution to arrest early childhood caries in preschool children

### Setting

Kindergartens in Hong Kong that have joined our outreach dental service will be invited to take part in this study. An invitation letter will be sent to the principals of kindergartens explaining the study’s purpose and procedures (Additional file 2). Any preschool children who have tooth decay will be invited to join the study. Written informed consent explaining the study’s purpose and procedures will be sought from their parents. A trained dentist and a dental assistant will go to the kindergartens to assess the caries-arresting effects of SDF with different application times on preschool children.

### Participants

The children included in the study should (a) be aged 3–5 years and attending kindergarten, (b) be generally healthy, (c) have parental consent, and (d) have untreated caries that extends into the dentine. Children who are uncooperative and difficult to manage, have major systemic diseases, or are on long-term medications will be excluded. If the participated child does not return for the follow-up examination, a project assistant will contact the parent and ask for will the reasons for drop out.

### Recruitment and screening

The University of Hong Kong is providing outreach dental care service to all 180,000 kindergarten children in Hong Kong (https://www.jccohp.hku.hk/). A research assistant will invite sufficient number of kindergartens for achieving adequate participant enrolment to reach the target sample size. A trained project assistant will explain the objectives and procedures of this study to the teachers of the participating kindergartens. The teachers will distribute an invitation letter and an informed written consent to the parents of children attending the first and second year of the kindergarten. The written consent will be collected from the parents before the trial takes place. Oral health education will be provided to the children in the participating kindergartens, followed by initial oral examinations. Trained field workers on the outreach team will recruit potential participants after the initial oral examinations.

### Clinical examination

The trained dentist will perform clinical examinations of the participating children in the kindergartens. The dentist will carry out a careful visual inspection with the aid of a World Health Organization (WHO) Community Periodontal Index (CPI) periodontal probe and a front-surface dental mirror with light-emitting diode intra-oral illumination [11]. The oral hygiene status will be measured using the visible plaque index (VPI). Both the buccal and the lingual surfaces of six index teeth (55, 51, 63, 71, 75, and 83) will be examined [12]. The presence or absence of visible plaque on the caries surface will also be recorded.

Tooth status (decayed, missing, filled surface [dmfs] score), tooth discolouration, and hyper-mobility will be recorded in the chart [13]. Teeth with carious lesions extending into the pulps, or signs suggesting that the teeth are non-vital, such as tooth discolouration, hypermobility, or abscesses, will not be included in this study. Dental caries will be diagnosed at the cavitation level. The carious lesion will be gently explored using a WHO CPI probe in the centre of the lesion [14]. Great care will be taken to avoid tooth damage during the probing. A carious lesion will be recorded as active if softness is detected, whereas if the dentine surface is hard to probe, it will be classified as an arrested caries [6, 12]. All surfaces (i.e., buccal, lingual, mesial, distal, and occlusal for the posterior teeth) of each tooth will be assessed. In addition, the colour of the carious lesion will be classified into one of four categories according to PANTONE colour plates (Table 2) placed next to the carious lesion [15]. The primary endpoint or outcome measure is active carious lesion at baseline that becomes arrested in the 6-month follow-up. The same dentist will serve as the examiner throughout the 6-month follow-up. Intra-examiner agreement on the plaque and caries assessment will be monitored and conducted in 10% of the children at each stage of the clinical trial.

**Table 2 Tab2:**
[figure not shown]
Coding for the colour assessment of dentine carious lesions

### Questionnaire survey

A validated parental questionnaire [3, 4] regarding children’s oral hygiene habits (daily tooth brushing frequency), parent-assisted tooth brushing, the main caretaker of the child, the use of toothpaste, the use of a bottle for feeding, bottle feeding before going to bed without brushing, daily snacking frequency, dental visits, the parental educational level, and the family’s total income will be administered at baseline. The questionnaire will also assess parental satisfaction with the child’s oral health and dental aesthetics. Another questionnaire survey will be conducted after 6 months.

### Randomisation and treatment allocation

The participating children with caries will first be categorised as either (1) having a high caries rate (or severe early childhood caries as defined by the American Academy of Paediatric Dentistry, 2008), which is defined as the presence of more than three untreated caries surfaces, or (2) having a low caries rate [16]. The children will be allocated via a stratified randomisation method with a block size of 18 into nine groups for the application of 38% SDF (Advantage Arrest Silver Diamine Fluoride 38%, Elevate Oral Care, FL, USA) on each carious lesion (Fig. 2):

**Fig. 2 Fig2:**
[figure not shown]
Flow diagram of the randomised clinical trial of the effects of 38% silver diamine fluoride (SDF) application time on arresting early childhood caries

Group 1 – A 3-s application

Group 2 – A 5-s application

Group 3 – A 10-s application

Group 4 – A 15-s application

Group 5 – A 30-s application

Group 6 – A 45-s application

Group 7 – A 60-s application

Group 8 – A 120-s application

Group 9 – A 180-s application

### Allocation concealment and implementation

The randomisation sequence will be generated by a computer by the statistician, who will maintain the random number sequence in opaque sealed envelopes to conceal the allocation sequence until the interventions are assigned. A dental assistant will open the envelope and assign the children to the treatment group according to the random number generated.

### Blinding

In this double-blind randomised clinical trial, a dental assistant will conduct the group allocation. The examiner and the child will not be informed of the treatment group allocation. Another operator will apply the SDF solution after the oral examination.

### Harms

A 24-h mobile contact number will be given to the parents of each child to call if there are any problems.

### Interventions

An independent operator will use a micro-brush (Advantage Arrest Applicators, Regular size, Elevate Oral Care, FL, US) to apply the 38% SDF solution. Each carious lesion will receive a single application of 38% SDF at different application times according to the allocated group. The amount of 38% SDF solution to be applied is approximately 0.004 mL [17]. The children will be instructed not to eat or drink for an hour after the SDF application. The carious surfaces will become hard and black if the treatment has successfully arrested the carious lesions. In case any harm occurs, the principal investigator will monitor the child and report the incident to the institutional review board (IRB). After the baseline examination, the research assistant will provide a report on the child’s oral health status to the parents. The report will feature a note asking the parents to report to the dentist if they notice any side effects on the treated tooth and the surrounding gingival tissue after SDF treatment.

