### Follow-up evaluation

The follow-up oral examinations will be conducted 6 months later in the kindergartens. The same examiner will perform the examinations using the same equipment, procedure, and diagnostic criteria as those used in the baseline examinations. Each child’s oral hygiene and caries status will be recorded. In addition, the presence of visible plaque and the statuses of the included carious surfaces will be assessed. The colour of the arrested caries lesion will be classified and recorded as well [15]. The dentist will also record any sign of a tooth’s non-vitality, such as tooth hypermobility and an abscess. The examiner will not serve as the operator for the fluoride application.

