### Post-trial care

All children will be under care through the outreach kindergarten service. Children who experience any side effects from the SDF application will be followed up by the outreach dentist.

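### Gingival and mucosal side effects are collected only by spontaneous parent report, so short-lived soft-tissue effects cannot be compared reliably across the 3 to 180 s arms

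*Protocol article*

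**What the plan says.** The protocol article deals with side effects in several places.

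- **Harms.** The section is one sentence: "A 24-h mobile contact number will be given to the parents of each child to call if there are any problems".
- **Interventions.** After the baseline examination, parents receive a report on the child's oral health: "The report will feature a note asking the parents to report to the dentist if they notice any side effects on the treated tooth". The same request covers the gum around the tooth. Once a harm is known, the principal investigator monitors the child and informs the review board. The operator's task is to apply the solution; no check of gum or mucosa is described.
- **Follow-up evaluation.** At 6 months the examiner records oral hygiene, plaque, caries status, the colour of arrested lesions and signs of non-vitality, "such as tooth hypermobility and an abscess". Gingival or mucosal irritation is not listed.
- **Questionnaire survey.** The listed items cover habits, diet, dental visits, family background and satisfaction with oral health and appearance. None is about side effects. For the later survey the text says only "Another questionnaire survey will be conducted after 6 months".
- **Outcome measure.** The follow-up interviews will ask about dental treatment received elsewhere.
- **Post-trial care.** "Children who experience any side effects from the SDF application will be followed up by the outreach dentist".
- **Ethical considerations.** A separate protocol for managing side effects exists, and all side effects go to the review board within 48 h. That protocol is not shown.

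**The concern.** Application time is the only thing randomised, and it runs from 3 s to 180 s. The trial hypothesises that longer application arrests more lesions, and its Discussion expects the result to help determine the optimal application time. Such a judgement sets benefit against burden. The Interventions section itself names the gum around the treated tooth as a place where side effects may appear.

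The method described for finding such effects is passive. Treatment takes place in the kindergarten, and the article does not say that a parent is present. The only scheduled examination after treatment is at 6 months, too late to see an effect that has already healed. If an unknown share of events goes unreported, a low count in the 120 s and 180 s arms carries little information, and a true gradient with time could be missed. The 48-h report to the review board can be no more complete than the detection that feeds it.

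**Working it through.** **1. Who looks or asks, and when**

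| Occasion | Recorded or asked by staff | Gingival or mucosal effects |
|---|---|---|
| Application (Interventions) | no soft-tissue check described | not listed |
| Days to months after (Harms, Interventions) | nothing active | if a parent notices and reports |
| 6-month examination (Follow-up evaluation) | plaque, caries, colour, hypermobility, abscess | irritation not listed; abscess is |
| Questionnaires (Questionnaire survey) | listed items | not listed |
| Follow-up interview (Outcome measure) | other dental treatment | not listed |

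Only the second row can capture a transient soft-tissue effect.

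**2. The plan's own arm size**

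Inputs from the sample size section: 104 surfaces per group before clustering, 4.75 surfaces per child, intraclass correlation 0.23, dropout 0.5%, non-compliance 10%.

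- Design effect: 1 + (4.75 − 1) × 0.23 = 1.8625.
- Surfaces: 104 × 1.8625 = 193.7. Children: 193.7 / 4.75 = 40.8, so 41; 41 × 4.75 = 194.75, so 195 surfaces.
- Recruited: 41 / (0.995 × 0.90) = 45.8, so 46 per group; 46 × 9 = 414.

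These match the article. It gives no figure for harms, so the rates and reporting fractions below are assumptions.

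**3. What zero reports in one arm would exclude**

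Let r be the fraction of events that are reported. With n = 46 children and none reported, the one-sided 95% upper limit for the reported risk is 1 − 0.05^(1/46) = 6.3%. The limit for the true risk is 6.3% / r.

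- r = 1: 6.3%
- r = 0.5: 12.6%
- r = 0.25: about 25%

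The 6.3% comes from the arm size and would remain with perfect capture. Only the widening beyond it comes from passive collection.

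**4. Chance of seeing at least one event in an arm, assumed true risk 5%**

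- Full capture: 1 − 0.95^46 = 0.91.
- A quarter reported: reported risk 0.05 × 0.25 = 0.0125, so 1 − 0.9875^46 = 0.44.

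**5. Power to see a gradient with time**

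Trend test with scores in seconds, 46 children per arm, one-sided 0.025, normal approximation, true risk rising linearly from 3 s to 180 s, same capture in every arm:

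| Assumed risk, 3 s to 180 s | Full capture | 50% | 25% | 10% |
|---|---|---|---|---|
| 2% to 10% | 69% | 46% | 30% | 19% |
| 2% to 15% | 91% | 68% | 46% | 28% |
| 5% to 20% | 88% | 62% | 40% | 23% |

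These are rough where few events are expected; for 2% to 10% at 10% capture, about 1.7 are expected in the whole trial.

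**The case against.** The strongest objection is that this is a condensed article. Case-report fields and adverse-event questions are usually left to the full protocol, and Ethical considerations cites a side-effect protocol, a monitoring system and continuous data review. Active collection in a document not shown cannot be ruled out. This stands as a limit on confidence. It does not remove the point, because the article states a method for soft-tissue effects and that method is passive. The unseen protocol is described in terms of management, alongside review-board reporting; both start once an effect is known.

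It can also be said that the questionnaire list describes the baseline survey and that the 6-month items are not given. That is fair: a side-effect item in the later survey is not described, but it is not excluded either.

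Four stronger readings may tempt a reader, and the article does not support them.

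- *All harms depend on parents.* The examiner records non-vitality, including abscess, and lesion colour. Staining by application time is the secondary objective. Both can be compared by arm.
- *The reporting routes contradict each other.* A telephone number, a request to tell the dentist, the principal investigator's duty to monitor and report, and care by the outreach dentist are compatible roles. What is unclear is who receives a parent's report.
- *Reports will unblind the examiner.* The article uses the term dentist for the examiner elsewhere ("The same dentist will serve as the examiner throughout the 6-month follow-up"), so a report might reach that person. But a parent's report need not reveal the seconds applied, and a different operator treats the child.
- *A child without a report is counted as unharmed.* No such analysis is stated.

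Finally, the objectives claim no soft-tissue safety comparison, and the primary endpoint, analysis and sample size are unaffected. This is correct and limits the weight of the point.

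**Conclusion.** The point holds in a narrow form. As the article describes it, gingival and mucosal side effects reach the trial only through spontaneous parent report, so short-lived effects cannot be compared reliably across application times. It would go too far to infer that the trial can say nothing about harm by arm, since non-vitality and staining are actively recorded.

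The size depends on how much parents report, which the article does not give. Under assumed fractions of one half and one quarter, an arm with no reports excludes a true risk only above 12.6% or 25%, against 6.3% with full capture. For an assumed gradient of 2% to 15%, trend power falls from about 91% to 68% or 46%. These figures illustrate the direction and rough scale; they do not predict harm rates. The conclusion also assumes that the side-effect protocol not shown adds no active detection. This is a cheap improvement worth making, not a threat to the primary result.

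**What to change.** 1. Turn the existing note to parents into a short tick-box slip: gum or mouth soreness, whitening or ulcer, tooth pain, swelling, none; date noticed. Every parent returns it through the kindergarten within a few days of treatment. The 'none' box separates no effect from no answer.
2. Have the operator or dental assistant record any immediate soft-tissue effect on the treatment sheet.
3. Put the same items in the 6-month parental questionnaire.
4. Tabulate by application time, with the number of responses as denominator. If 41 slips came back in an arm of 46, zero events would exclude a risk above 1 − 0.05^(1/41) = 7.0%, which is close to the 6.3% for complete return.
5. State who receives parents' slips and calls, preferably someone other than the blinded examiner.
6. If the side-effect protocol already provides for active detection, say so in the Harms section.

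The cost is one printed slip, an entry on the treatment sheet and a few questionnaire items; teachers already distribute study papers to parents. More minor effects will be reported, and some slips will not come back. The target of 414 children does not change.
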